**Methods:**

Design: A two-arm cluster randomized clinical trial of 30 Primary Health Care Centers (PHCC) in Mallorca (Spain), in which each center was randomized to an intervention arm or a usual care arm. We expect that the number of patients identified as suitable for PC (including non-oncological PC) is at least 5% greater in the intervention arm.

Sample size: A total of 4640 deceased patients. Outcomes will be assessed by a blinded external review of the electronic records.

Interventions: General practitioners (GPs) and nurse leaders in PC for each PHCC will be appointed. These leaders will help promote PC training of colleagues, improve symptom management and psychological support of patients, and evaluate the complexity of individual cases so that these cases receive assistance from PC home-based teams.

Measurements: Early identification (>90 days before death), evaluation of case complexity, level of case complexity (with referral to a home-based PC team), use and cost of hospital and primary care services, and quality of life during the last month of life (≥2 emergency room visits, ≥2 hospital admissions, ≥14 days of hospitalization).

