### Randomization

Each of the 30 participating primary health care centers will be randomly assigned to the intervention or control group. Randomization and concealment will be centralized, through a single coordinating center, using a computer-generated block randomization in blocks of six.

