### Sample size

It is necessary to prospectively analyze 4640 clinical records of deceased patients from the defined population (causes of death: ICD codes C00-C97; 100–152, 160–169, N17, N18, N28, 112, 113, K70-K77, J06-J18, J20-J22, J40-J47, J96, G10, G20, G35; G122, G903, G231.F01, F03, G30, R54, B20-B24) to detect an increase of at least 5% in the proportion of patients identified as needing PC at 1 month before death in the intervention arm, assuming that 12% of patients will need PC in the control arm, a median of 263 patients in each health care center (cluster size), and an intra-class correlation coefficient of 0.015 [34].

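### The total of 4640 records, the cluster size of 263 and the 30 centres do not fit together, and 4640 does not follow from the stated inputs

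*Protocol article*

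**What the plan says.** The Sample size section of the protocol article opens: "It is necessary to prospectively analyze 4640 clinical records of deceased patients from the defined population". The aim, for the centres given a leader, is "to detect an increase of at least 5% in the proportion of patients identified as needing PC at 1 month before death". The control proportion enters as "assuming that 12% of patients will need PC in the control arm". For clustering, the section takes "a median of 263 patients in each health care center (cluster size), and an intra-class correlation coefficient of 0.015 [34"]. It gives no alpha, sidedness or power.

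The number of centres is fixed elsewhere. The Randomization section says: "Each of the 30 participating primary health care centers will be randomly assigned to the intervention or control group". The Setting section agrees, with 14 centres in one evaluated district and 16 in the other. The abstract repeats both the 30 centres and the total of 4640, and words the effect as follows: "We expect that the number of patients identified as suitable for PC (including non-oncological PC) is at least 5% greater in the intervention arm".

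**The concern.** Total, number of clusters and cluster size are linked by one multiplication, and here the product is far from the stated total. The design effect depends on the cluster size, so the conflict carries into the calculation: a reader cannot tell whether 4640 was inflated for about 155 records per centre, for 263, or for some other number.

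This paragraph is the only justification of the trial's size. As printed, it does not tell the reader what power the 30-centre design has for the effect it names.

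**Working it through.** **Inputs.** From the Sample size section: total 4640, control proportion 12%, increase of 5% (read as 12% to 17%), median cluster size 263, ICC 0.015. From the abstract and the Randomization section: 30 centres. Assumed, because not stated: equal allocation, and the alpha, sidedness and power shown at each step.

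**Step 1. Do the three counts agree?** No alpha or power is needed here.
- 30 × 263 = 7,890, not 4640.
- 4640 / 30 = 154.7 per centre, not 263.
- 4640 / 263 = 17.6 centres, not 30.

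The article calls 263 a median, so it need not equal the mean. If 15 of the 30 centres hold 263 each, they account for 15 × 263 = 3,945 records. The other 15 then share 4640 − 3,945 = 695, or about 46 each, and fewer if the larger centres exceed 263. That is possible on paper but not a sensible reading.

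**Step 2. Can 4640 be reproduced from the stated inputs?**
- Design effect: 1 + (263 − 1) × 0.015 = 4.93.
- Sum of variances: 0.12 × 0.88 + 0.17 × 0.83 = 0.2467.
- Per arm without clustering, two-sided 5%, 80% power: (1.96 + 0.8416)² × 0.2467 / 0.05² = 774.5. The pooled-variance formula gives 778.
- Total: 2 × 774.5 × 4.93 = 7,637, or 2 × 778 × 4.93 = 7,671.

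Other settings at 263 per centre (unpooled to pooled formula):

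| Setting | Total records |
|---|---|
| Two-sided 5%, 90% power | 10,224 to 10,264 |
| Two-sided 5%, 80% power | 7,637 to 7,671 |
| One-sided 5%, 80% power | 6,016 to 6,044 |
| One-sided 5%, 70% power | 4,579 to 4,605 |

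Only the last row comes near 4640. Two-sided 10% with 70% power is the same calculation.

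**Step 3. What would produce 4640?** At two-sided 5% and 80% power, the design effect would have to be 4640 / (2 × 774.5) = 2.995, which means (2.995 − 1)/0.015 + 1, or about 134 records per centre. The article contains no such figure.

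**Step 4. Power of the two coherent 30-centre designs** (two-sided 5%, 12% against 17%).
- 4640 records, 154.7 per centre: design effect 1 + 153.7 × 0.015 = 3.305. SE = √(3.305 × 0.2467 / 2320) = 0.01875, and 0.05 / 0.01875 = 2.667. Power is about 76%, or about 73% with t on 28 df. The difference detectable with 80% power is about 5.3 points. Reaching 80% for 5 points would take 2 × 774.5 × 3.305, or about 5,120 records.
- 7,890 records, 263 per centre: SE = √(4.93 × 0.2467 / 3945) = 0.01756, and 0.05 / 0.01756 = 2.848. Power is about 81%, or about 78% with t on 28 df.

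**The case against.** The strongest reply is that the article states neither alpha nor power. In a condensed article that omission is no finding, so any claim of shortfall depends on supplied values. The aim is also worded as an increase, and a two-sided test is named only for the baseline comparisons. With one-sided 5% and 155 records per centre, 85% power needs about 4,690 records, so 4640 would give about 85%. At 263 per centre, one-sided 5% with 70% power nearly reproduces 4640. This stands to the extent that every power figure above is conditional. It does not remove the conflict. Step 1 uses no alpha or power, the 85% case has to abandon the stated 263, and the 70% case is unconventional, stated nowhere, and at 263 per centre corresponds to about 18 centres.

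Three stronger readings are tempting, and the documents do not support them:
- That the 5-point effect is itself wrong, or that the trial is short by about 3,000 records. If 263 per centre is right, 30 centres supply 7,890 records, the effect has about 81% power, and only the printed 4640 is wrong.
- That a null result would be over-interpreted. Nothing in the article ties interpretation to the planned power. The records are those of eligible deaths in a fixed window, so the achieved number is set by mortality and not by recruiting to a target.
- That the abstract plans for a relative 5% increase. From 12% to 12.6%, at a design effect of 4.93, this would need about 464,000 records. The Sample size section refers to an increase in the proportion, so percentage points must be meant. This is a matter of wording.

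**Conclusion.** The point holds as an internal inconsistency and a sample-size figure that cannot be reproduced. The total, the cluster size and the number of centres cannot sensibly all stand, whatever alpha and power were used. With the stated inputs and conventional settings, the requirement at 263 per centre runs from about 6,020 (one-sided 5%, 80% power) to about 10,260 (two-sided 5%, 90% power). The standard case of about 7,640 to 7,670 is some 65% above 4640.

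The documents do not show whether 4640 or 263 is the error. At two-sided 5%, the practical consequence is modest either way: 73% to 76% power if 4640 over 30 centres is right, and 78% to 81% if 263 per centre is right. These figures assume equal arms, equal centre sizes and the stated ICC.

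**What to change.** Restate the Sample size section as one coherent set: 30 centres, expected eligible deaths per centre in the death window, the resulting total, alpha, sidedness and power. Make the total in the abstract match.

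- If 4640 over 30 centres is the expected number, replace 263 by about 155. State the power this gives (about 76%, or 73% with t on 28 df, at two-sided 5%) or a detectable difference of about 5.3 points.
- If 263 per centre is right, replace 4640 by about 7,890 and state about 81% power (78% with t).

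In the same edit, word the effect as 5 percentage points (12% to 17%) in both places.

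The cost is one paragraph and a line or two of the abstract. In the first case the stated power is slightly less favourable than a conventional 80%. No extra centres or patients are needed.

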### Statistical analysis

The effectiveness of the intervention will be evaluated by a prospective analysis of early patient identification for PC and resource utilization. Categorical baseline variables, at the patient level, from centers in the control and intervention groups will be compared using a 2-sided cluster-adjusted chi-squared test. The total number of admissions to a hospital or emergency room, visits to primary care, and total costs will be compared using Somers’ D rank correlation coefficient.

The estimated relative risk (RR) of being identified after the primary care intervention will be adjusted for cluster by a log link in a binomial distribution of a robust generalized estimating equation (GEE), with an exchangeable correlation structure. The absolute risk reduction (ARR) and number needed to treat (NNT) will be calculated from the RR.

We will conduct a multivariable regression analysis using a GEE, and determine a gamma distribution and log link to estimate the effectiveness of the intervention on health care costs.

A subgroup analysis will be used to determine the effectiveness of the intervention on the percentage of non-cancer patients identified as needing PC based on evaluation of case complexity. This procedure will analyze 3 different illness trajectories (cancer, organ failure, or dementia/frailty). The differential effectiveness of the intervention in these patients will be identified as a statistically significant interaction of the proposed variables with treatment efficacy.

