### Setting

IB Salut is a public health organization in the Spanish National Health System, in which universal tax-funded health care services are provided to every citizen, and services are free at the point of access. Each patient is registered with one primary health care center. The Balearic Health Care Service covers the entire population of the Balearic Islands. Majorca is the largest island (850,000 inhabitants), and has four health districts (North, South, East and West Health Districts), each of which has a general hospital and several primary health care centers. PC services in Mallorca Island are provided by 3 PC units in non-acute hospitals and a PC home-based service, with 7 teams of physicians, nurses, and psychologists.

Primary health care centers from 3 health districts in Majorca will participate in the study. The intervention will be managed in the North Health District, which has 6 primary health care centers.

The intervention will be evaluated in 2 health districts: the South Health District (264,757 inhabitants), which has a university hospital and 14 primary health care centers, and the East Health District (326,988 inhabitants), which has a general hospital and 16 primary health care centers.

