### Data collection

Early identification of patients, resource utilization, and place of death will be estimated relative to the number of patients who could benefit from PC services (causes of death: ICD codes C00-C97; 100–152, 160–169, N17, N18, N28, 112, 113, K70-K77, J06-J18, J20-J22, J40-J47, J96, G10, G20, G35; G122, G903, G231.F01, F03, G30, R54, B20-B24), using the calculation of the potential population size for PC developed by Rosenwax [8, 9]. The causes of death will be identified by review of the death certificates of patients who died 9 to 21 months after the onset of PC.

The NECPAL and IDC-PAL are integrated in the electronic records of GPs, thereby allowing early identification of patients needing PC and evaluation of case complexity. We will extract data from the electronic records upon completion of the NECPAL to identify the need for PC, estimate case complexity using IDC-PAL, and record all emergency department visits, outpatient office visits, primary care visits, duration of all hospital stays, and ICU admissions.

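### The primary relative risk has no covariate beyond clustering, although centres from two districts were allocated with no district stratum stated; prespecifying district would be a cheap improvement, not the repair of an error

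*Protocol article*

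**What the plan says.** All places are in the protocol article.

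- **Primary model (Statistical analysis):** "The estimated relative risk (RR) of being identified after the primary care intervention will be adjusted for cluster", using a log-link binomial GEE with exchangeable correlation and robust variance. Clustering is the only adjustment named. The absolute risk reduction and number needed to treat are to be derived from the relative risk.
- **Costs (same section):** "We will conduct a multivariable regression analysis using a GEE, and determine a gamma distribution and log link to estimate the effectiveness of the intervention". This is the only outcome for which a multivariable model is stated.
- **Baseline variables (same section):** "Categorical baseline variables, at the patient level, from centers in the control and intervention groups will be compared using a 2-sided cluster-adjusted chi-squared test". The variables are not listed.
- **Illness trajectory (same section):** used in a subgroup and interaction analysis. "This procedure will analyze 3 different illness trajectories (cancer, organ failure, or dementia/frailty".
- **Allocation (Randomization):** centralised, "using a computer-generated block randomization in blocks of six". No stratification is stated.
- **Districts (Setting):** "The intervention will be evaluated in 2 health districts". South has 14 centres and a university hospital; East has 16 centres and a general hospital.

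**The concern.** District is known for every centre before allocation, and the two districts have different hospitals. Yet district appears neither in the stated randomisation nor in the primary model. With about 15 centres per arm, one arm may by chance hold clearly more South centres. If identification differs between districts, the estimate from that particular allocation shifts, and the unadjusted analysis carries the shift as extra variance. Significance tests of baseline variables do not help: they do not change the estimate, and under randomisation such differences arise by chance. At stake is some precision, and how readily a reader can trust the estimate if the districts turn out unbalanced.

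**Working it through.** **The plan's own figures.** The protocol gives no figure for the gain from covariates, so there is none to reproduce. Its inputs on precision (Sample size section) are 4640 deaths, 12% identified in the control arm, an increase of 5 (read as percentage points), cluster size 263 and intra-class correlation 0.015. With two-sided 5% and 80% power, which are assumed because neither is stated, these give 2 × 778 × (1 + 262 × 0.015) = 2 × 778 × 4.93 = 7671, not 4640. That is a separate question and is not used as support here.

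**Step 1: chance of district imbalance.** Five blocks of six, taken as 1:1 within blocks, give 15:15. If the order of centres was unrelated to district, the number k of South centres in the intervention arm has probability C(14,k) × C(16,15−k) / C(30,15).
- k = 9: 2002 × 8008 / 155,117,520 = 0.1034
- k = 10: 1001 × 4368 / 155,117,520 = 0.0282
- k = 11 and k = 12: 0.0043 and 0.0003

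The opposite tail is equal. A 9:5 split or worse has probability 2 × 0.1362 = 0.27; 10:4 or worse has 2 × 0.0328 = 0.07. If centres were instead listed by district before allocation, 12 of the South centres would fill two whole blocks (6:6), and the split could be no worse than 8:6. The protocol does not say which was done.

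**Step 2: what a 9:5 split does.** With equal centre sizes, the South share is 9/15 in one arm and 5/15 in the other. The risk difference shifts by (9/15 − 5/15) × d, where d is the district difference in identification. No value of d is given. Assumed values:
- d = 2 points: 0.53 points, 11% of the 5-point target
- d = 5 points: 1.33 points, 27% of the target

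**Step 3: precision from district alone, in closed form.** Take 4640/30 = 154.7 deaths per centre and a 12% risk. On the log scale:
- between-centre variance: 0.015 × 0.88/0.12 = 0.110
- within-centre variance: 0.88/(0.12 × 154.7) = 0.047
- total: 0.157

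A district rate ratio R contributes (14/30)(16/30)(ln R)² = 0.249 (ln R)². Estimating district costs a factor of about 28/27 = 1.037. If the district effect is part of the stated intra-class correlation, the variance ratio (adjusted/unadjusted) is (1 − contribution/0.157) × 1.037:
- R = 1: 1.04
- R = 1.2: (1 − 0.0083/0.157) × 1.037 = 0.98
- R = 1.5: (1 − 0.0409/0.157) × 1.037 = 0.77

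If the district effect comes on top of that correlation, R = 1.5 gives 0.157/(0.157 + 0.041) × 1.037 = 0.82. In the first case break-even is at a contribution of 0.157 × (1 − 1/1.037) = 0.0056, that is ln R = √(0.0056/0.249) = 0.15, or R of about 1.16.

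**Step 4: simulation with district and trajectory both in the model.** 30 centres of 155 deaths, intra-class correlation 0.015, log-link exchangeable GEE with uncorrected robust standard errors, 1000 runs per scenario. The prognostic strengths are assumptions.

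| Scenario | Variance ratio, adjusted/unadjusted | Power, unadjusted to adjusted | Null rejection at nominal 5%, unadjusted to adjusted |
|---|---|---|---|
| Neither prognostic | 1.04–1.05 | 77% to 77% | 7.2% to 8.2% |
| Cancer 2×, district 1.2 | 1.02 | 73% to 75% | 7.5% to 9.0% |
| Cancer 4×, district 1.56 | 0.72–0.74 | 63% to 76% | 7.9% to 8.5% |

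Monte Carlo error of the rejection rates is about 0.8 points. Step 3 shows that district alone accounts for most of the gain in the last row, so trajectory adds little. The log-binomial GEE converged in all runs tried (80 in each of three scenarios).

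**The case against.** The strongest reply is that nothing here is wrong. Centres are randomised, and a GEE with clustering and robust variance is a valid analysis. Chance imbalance in district is random error that the between-centre variance already reflects; it is not bias. A condensed article may also leave its covariate list to a full protocol or analysis plan, and nothing in the text excludes an adjusted analysis. The first part stands in full. The second stands in part: the article does state the primary model and names multivariable modelling only for costs, so the text as it stands describes a cluster-only primary analysis.

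A reader might infer more than the documents support:
- **That adjustment removes imbalance, gains precision and costs nothing.** It corrects only for modelled covariates. The gain depends on associations that the documents do not give, and with weak or moderate associations precision hardly changes. A degree of freedom is lost, and the already raised type I error may rise slightly.
- **That a variance cut of about a quarter can be expected.** This needs a district rate ratio near 1.5, for which there is no source.
- **That trajectory belongs in the primary model as a baseline covariate.** It rests on cause of death: "The causes of death will be identified by review of the death certificates of patients who died 9 to 21 months after the onset of" palliative care. That is recorded after randomisation. The same causes already define the analysis population, so the assumption involved is not wholly new, but it should be stated. Nor is trajectory only tested for balance, since it has an interaction analysis.
- **That age and sex are available for adjustment.** Neither is listed in Data collection; age appears only as the threshold of 18 years in the primary outcome.
- **That allocation should be stratified by district.** The abstract reports randomisation as already done, so this is too late.

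**Conclusion.** The point holds as a modest improvement. The stated primary model omits district, and a 9:5 or worse South split has a chance of about 27%, provided that the order of allocation was unrelated to district. The cluster-only relative risk is valid, so its conclusions would not be invalid without the change. The effect on precision is unknown from the documents. Under the assumed scenarios, with district and trajectory both modelled, it runs from about 5% more variance (neither prognostic) to about 28% less (district rate ratio about 1.5); by the closed form, district alone roughly breaks even near a rate ratio of 1.16. The case for adjustment is therefore protection against a plausible imbalance at small cost, not a promised gain in power.

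**What to change.** Before outcome data are examined:

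1. Specify the primary GEE as arm plus health district, clustered by centre, with Poisson and robust variance as the named fallback if the log-binomial fit fails.
2. Obtain the relative risk and the absolute difference by standardising predicted risks over the district mix of the whole sample. With a log link and no interaction, the standardised relative risk equals the exponentiated arm coefficient; the absolute difference then comes from the same model.
3. Report the cluster-only relative risk as a sensitivity analysis.
4. If wanted, add illness trajectory in a prespecified supporting model, stating the assumption that the intervention does not affect the cause recorded on the death certificate.
5. Apply a small-sample correction to the robust standard errors (for example Mancl–DeRouen or Kauermann–Carroll, with a t reference). Simulated error rates were above 5% with or without adjustment, so this is worth doing either way.

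The cost is a change of analysis wording, one between-centre degree of freedom (about 28 to 27) and a slight loss of precision if district proves irrelevant. No new data or patients are needed.

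### The plan adjusts the baseline test and the primary relative risk for cluster but states no cluster adjustment for the Somers' D comparisons of admissions, visits and costs; a smaller gap is that no few-cluster correction is named for the GEE.

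*Protocol article*

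**What the plan says.** The unit of randomisation is the centre: "Each of the 30 participating primary health care centers will be randomly assigned to the intervention or control group" (Randomization), by "computer-generated block randomization in blocks of six". Five blocks of six, balanced within block, imply 15 centres per arm; the article does not state the ratio.

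The Statistical analysis section then deals with clustering unevenly:

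- **Baseline categorical variables:** a two-sided chi-squared test, stated to be adjusted for cluster.
- **Admission totals, primary care visits and total costs:** the next sentence ends "total costs will be compared using Somers’ D rank correlation coefficient". It mentions neither clustering nor a standard error.
- **Primary relative risk of identification:** "adjusted for cluster by a log link in a binomial distribution of a robust generalized estimating equation (GEE), with an exchangeable correlation structure". No small-sample correction and no reference distribution is named.
- **Costs, second analysis:** a multivariable GEE with gamma distribution and log link. Neither a robust variance nor a correlation structure is repeated there.

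Total hospital admissions, total emergency admissions and cost in the final month of life are listed secondary outcomes. The Sample size section gives an ICC of 0.015, in the context of patient identification only.

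**The concern.** A comparison between randomised centres has to carry the between-centre variation in its standard error. The section says so for a descriptive baseline test and for the primary outcome, yet not for the outcome comparisons named in the sentence between them. An analyst who follows that sentence literally could use a default Somers' D or rank-sum standard error, with every deceased patient counted as independent.

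At stake are the conclusions on resource use, which the Background and Discussion present as a main purpose of the intervention. For admission and visit totals no clustered analysis stands beside Somers' D as a check.

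The second, lesser matter is the number of clusters. The ordinary sandwich variance is biased downward with 15 centres per arm, and a normal reference ignores that only 30 − 2 = 28 degrees of freedom are available. Together they would make the primary test slightly liberal.

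**Working it through.** **The plan's own figures.** The article states no type I error, so there is no figure of that kind to reproduce. Its one related figure is the sample size: "It is necessary to prospectively analyze 4640 clinical records of deceased patients". For 12% against 17%, with assumed two-sided 5% and 80% power (neither is stated), 778 per arm are needed before clustering. With 263 per centre and ICC 0.015 the total is 1556 × 4.93 = 7671, not 4640. That mismatch does not bear on this point, but it leaves the centre size open. Both values are therefore used: 4640/30 = 154.7 and 263.

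**Inputs from the article:** 30 centres; 12% control proportion; ICC 0.015 for identification. **Assumed:** 15 centres per arm; nominal two-sided 5%; ICC of the resource outcomes 0.005 to 0.05; coefficient of variation (CV) of centre size 0 to 0.65.

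**1. Somers' D with patient-level standard errors, by formula.** The design effect is DE = 1 + (m − 1) × ICC, and the actual error of a nominal 5% test is 2 × [1 − Φ(1.96/√DE)].

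| ICC | m | DE | √DE | 1.96/√DE | Type I error |
|---|---|---|---|---|---|
| 0.005 | 154.7 | 1.77 | 1.33 | 1.474 | 14% |
| 0.005 | 263 | 2.31 | 1.52 | 1.290 | 20% |
| 0.015 | 154.7 | 3.305 | 1.82 | 1.078 | 28% |
| 0.015 | 263 | 4.93 | 2.22 | 0.883 | 38% |

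**2. The same by simulation.** The formula is for means, so a rank comparison was also simulated under no effect: 15 against 15 centres, a skewed outcome with many ties, 2,000 runs per setting.

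| ICC | m | Patient-level SE | Centre-level SE, z test |
|---|---|---|---|
| 0.005 | 155 | 12.0% | 5.7% |
| 0.005 | 263 | 16.2% | 5.8% |
| 0.015 | 155 | 25.0% | 6.0% |
| 0.015 | 263 | 34.5% | 5.8% |
| 0.05 | 155 | 45.5% | 5.5% |
| 0.05 | 263 | 55.1% | 5.6% |

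The ICC here is on an underlying normal scale, and coarsening to tied counts would be expected to dilute it, which would explain values a little below the formula. A further simulation gave 14–17% at ICC 0.005 and 28–36% at 0.015.

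**3. The primary GEE with 30 centres.** With equal centre sizes, the uncorrected sandwich divides by 15 where 14 would be unbiased, so the standard error is short by √(14/15) = 0.966. The effective critical value is 1.96 × 0.966 = 1.894, and 2 × P(t on 28 df > 1.894) = 6.9%. Of the excess, one point comes from the reference alone: 2 × P(t on 28 df > 1.96) = 6.0%.

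Simulation under no effect used beta-binomial data, 12%, log link and exchangeable correlation, with 15,000 to 20,000 runs per setting:

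- Uncorrected robust, z test: 6.6–7.7%.
- Uncorrected robust, t on 28 df: 5.9–6.7%.
- Kauermann-Carroll correction, t on 28 df: 4.9–5.6%.
- Mancl-DeRouen-type leverage correction, t on 28 df: 4.4–4.9%.

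**The case against.** The best reply is that the article is silent rather than wrong. It names a statistic and no standard error; Somers' D can be computed with a clustered variance; and adjustment elsewhere in the same section shows that the authors knew of the issue. This stands against the stronger reading that a reader might infer, namely that the plan treats patients as independent and that its tests are therefore too liberal. The text does not say that. It does not remove the gap: the article gives this detail for the neighbouring analyses and omits it here.

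Other parts of the reply also stand:

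- Costs are not left without a GEE, so the exposure falls mainly on admission and visit totals.
- The ICC of 0.015 belongs to identification. Applied to resource use it is borrowed, and the true inflation is unknown.
- A reader might infer that the cost GEE uses the same uncorrected sandwich. The cost sentence does not say so.
- A bias-corrected sandwich is still a robust GEE, and the choice of correction and reference is often left to a full protocol or analysis plan, which is not shown. Alone, the GEE matter would not amount to an error in the article.

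**Conclusion.** The point holds as an omission with conditional consequences. Cluster adjustment is stated for the baseline test and the primary relative risk, and not for Somers' D, which is the only named analysis of admission and visit totals. If patient-level standard errors were used, type I error would be about 12–17% in simulation at ICC 0.005 (14–20% by formula) and 25–38% at 0.015 over both methods. These ranges rest on assumed ICCs, 15 centres per arm and 155 to 263 patients per centre. With centre-level standard errors the same comparison runs at 5.5–6.0% even with a z test, so the missing clause decides whether the results can be relied on.

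The primary analysis is clustered and is not in doubt for this reason. If its variance is left uncorrected with a normal reference, its error is about 7% instead of 5%, which is modest and easily removed.

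**What to change.** In the Statistical analysis section, state that Somers' D for admissions, primary care visits and costs is computed with centre as the cluster in its variance, and that tests and intervals use t on 28 degrees of freedom (centres minus 2, if all 30 are analysed and arm is the only centre-level term).

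As a smaller addition, state that the GEE analyses of the relative risk and of costs use a bias-corrected sandwich variance, for example Kauermann-Carroll, with the same reference.

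This takes two sentences and software options, with no new data or design change. For the GEE with equal centre sizes, intervals widen by about 8%: (2.048/1.96) × √(15/14) = 1.08. For Somers' D, intervals widen relative to a patient-level calculation by roughly √DE, that is 1.3 to 2.2 over the ICCs of 0.005 and 0.015, before the small t adjustment. That width reflects the between-centre variation that the design contains.
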